#### 2.8.1. Primary Outcome: Assessment Scales for PD Pain

The KPPS is a self-reported questionnaire that assesses pain in PD. Fourteen items in seven domains encompass recognized categories of pain in PD: domain 1, musculoskeletal pain; 2, chronic body pain; 3, fluctuation-related pain; 4, nocturnal pain; 5, orofacial pain; 6, discoloration/edema, swelling; and 7, radicular pain. Each item is scored by multiplying the scores of the intensity (0–3) by frequency (0–4), and the total score ranges between 0–144. The KPPS is a reliable and valid scale for grading various types of pain in PD [18]. In addition, the cut-off points for distinction of pain severity levels (no pain, mild, moderate, and severe pain) in PD have been reported for the KPPS [19]. In this study, the total KPPS score, including all seven domains, was measured to assess the improvement of direct PD-related pain.

#### 2.8.2. Secondary Outcomes: Evaluation Instruments of Pain and Related Symptoms

An NRS was used to assess the intensity and location of pain symptoms in each body part. Furthermore, given that pain is reportedly associated with negative emotions in PD [6,7], pain-related symptoms including depression, anxiety, and sleep disorders were assessed using questionnaire surveys, such as the Beck Depression Inventory II [20,21], Beck Anxiety Inventory [22,23], Pain Catastrophizing Scale [24], and PD Sleep Scale-2. Pain in PD can greatly reduce patient quality of life, and thus, the change in quality of life according to pain modulation was assessed using the Euro-Quality of Life-5 Dimension [25]. In addition, changes in motor and non-motor symptoms of PD due to pain modulation were evaluated using the UPDRS II and III.

### 2.9. Exploratory Outcomes

#### 2.9.1. Investigating Therapeutic Mechanisms and Biomarkers for PA to Treat PD Pain: Molecular Analysis and Neuroimaging Using MRI

The understanding of the neural basis of pain has increased with the development of neuroimaging techniques. Neuroimaging measurements using MRI could support the understanding of the neurophysiology of pain in patients with PD. In this study, we used a 3.0T MRI scanner (3T Philips, Achieva, whole-body MRI scanner) with a head coil to acquire structural and functional brain data. MRI scans included anatomical T1-weighted imaging, T2*-weighted echo-planar imaging sequence scans obtained by diffusion tensor imaging (DTI), and resting-state functional MRI (rs-fMRI). Regional gray matter volume and cortical thickness were assessed using T1-weighted images, and white matter microstructure changes were analyzed using DTI data. Resting-state fMRI data were used to calculate estimates of functional connectivity using independent component analysis and the seed-based correlation approach.

Additionally, an investigation of changes in blood molecular markers could help us to understand the mechanism of action of PA on pain in patients with PD. The levels of transcriptomic alterations and methylation; inflammation-related cytokines such as interleukin (IL)-1β, IL-2, IL-4, IL-6, and IL-10; tumor necrosis factor-α; interferon-gamma; cortisol; and C-reactive protein were analyzed. Blood was collected from the subjects and centrifuged at temperatures below 4 °C. The obtained plasma and serum samples were stored at temperatures below −80 °C until further analysis. The samples were analyzed at the Korea Institute of Oriental Medicine.

#### 2.9.2. Investigation of the Distribution of SD for PD Pain and SD Changes following PA: SD Questionnaire Survey

A personalized approach in complementary and alternative medicine, including traditional medicine, is suitable for the treatment of PD pain, which can be categorized into several types [26]. In a previous study, the most frequent symptom patterns of PD were *Yin* deficiency of the kidney and liver, deficiency of *Qi* and blood, phlegm heat and wind stirring, blood stasis and wind stirring, and deficiency of *Yin* and *Yang* [27]. However, the distribution of SD in PD patients with pain symptoms has not been reported. Therefore, we intended to identify the pathogenesis and present a complementary and alternative medicine treatment guide by investigating cold-heat and deficiency-excess SD for pain in PD. The cold-heat and deficiency-excess SD questionnaire was sufficiently verified through item reliability evaluation, correlation coefficient analysis, and factor analysis in healthy participants in South Korea [28,29]. The findings can be a basic study in the standardizing of SD for PD pain.

#### 2.9.3. Objective Evaluation of PA for PD Pain-Related Symptoms: Gait Analysis and Assessment of Facial Expressions in Response to Emotion-Eliciting Stimuli

To assess behavioral alternations and emotional dysregulation due to pain, we tested facial expressions in response to emotion-eliciting stimuli. Facial movements were recorded using a webcam, while participants watched video clips designed to elicit specific emotional valence (i.e., joyful, sad, appetite-inducing, anxiety-inducing, and neutral). The experimental protocol was implemented based on procedures from previous studies [30,31,32]. The iMotions software (version 7.0; iMotions Inc., Boston, MA, USA) was used to quantify the probabilistic scores for 17 facial action units, which were extracted from the video recordings of participants’ faces. Facial expressions were defined as a combination of facial action units, and we evaluated the “emotional contagion” of the feelings of others.

Increased frequency of pain in PD is associated with increased motor fluctuations and freezing of gait and rigidity [33]. Therefore, changes in gait analysis according to pain modulation were measured using the objective gait parameter wearable devices G-walk and Beflex. G-walk (BTS Bioengineering S.p.A., Garbagnate Milanese, Italy) is a system that wirelessly measures and analyzes the subjects’ walking and functional performance using acceleration, gyro sensors, and magneto sensors. Velcro is used to fix the device to the height of the fifth lumbar spine, and the subject is allowed to walk in this state. Gait is evaluated using various methods with the seven built-in protocols, and information such as acceleration, rotation (angle), and direction of patient movement is collected as three-axis data. In addition, the stance/swing phase is classified by detecting the increase or decrease in acceleration according to heel-ground contact, and force values such as the take-off force and propulsion are calculated using the patient’s weight and acceleration. The parameters are wirelessly transmitted through Bluetooth to the BTS G-Studio software for analysis. Beflex (B-Lab system; Beflex, Daejeon, Taejon-jikhalsi, South Korea) is a wearable earphone device that can perform professional gait analysis only using motion information from the patient’s head, and can estimate the ground reaction force and obtain gait factor data with high accuracy. It enables the analysis of indicators such as walking cadence, head angle, stride width, vertical amplitude, left and right amplitudes, left and right balance, impact, maximum force, leg stiffness, and consistency.

### 2.10. Safety Assessment and AEs

A clinical laboratory examination was performed at baseline, before treatment, and 8 weeks after completing treatment (visit 18) as a safety assessment for all participants. All AEs, defined as undesirable and/or unexpected medical findings that were absent prior to commencing this clinical trial, were recorded. AEs were reported to the institutional review board (IRB) of Kyung Hee University Hospital at Gangdong, which determined whether the trial should be discontinued. The causal link between AEs and the procedure was categorized into six stages as determined by the research clinician: Definitely related, Probably related, Possibly related, Probably not related, Definitely not related, and Unknown. Appropriate treatment and follow-up were provided for severe AEs (SAEs).

### 2.11. Statistical Methods

#### 2.11.1. Sample Size Calculation

This study was a pilot clinical trial to determine the degree of symptomatic improvement that can be achieved with PA treatment in PD patients. Because of the lack of difference between the PA treatment group and the conventional treatment control group, the effect size was assumed based on similar previous studies, such as MA and bee venom acupuncture [34,35,36]. Accordingly, with a significance level of 5% and 80% power, the effect size was assumed to be 1.21. Considering a dropout rate, the calculated target sample size was 30 subjects per group.

#### 2.11.2. Statistical Analysis

A complete set analysis was used to analyze the effectiveness of the intervention, and the per-protocol analysis was verified. For efficacy analysis, the mixed-effects model for repeated measures method was used, with each group and visit time as fixed factors and subjects as random factors. Student’s paired t-test or Wilcoxon signed rank test were used to compare factors before and after treatment within groups. All AEs, including SAEs, were classified by study group. All statistical analyses were performed using SAS^®^ version 9.4 (SAS Institute. Inc., Cary, NC, USA), and all *p*-values were two-sided. Statistical significance was set at a 5% level.

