### 2.2. Study Design and Setting

This clinical study was a pragmatic randomized, usual care (UC)-controlled, three-arm trial to investigate the effectiveness of PA for the treatment of pain in patients with PD. PD patients who meet the eligibility criteria will be enrolled and randomly allocated to the treatment group (PA with conventional therapy), manual acupuncture (MA) control group (MA with conventional therapy), or UC control group (UC with conventional therapy). The subjects underwent PA or MA 2 days per week for 8 weeks and were followed up for 4 weeks after treatment. All assessments were performed in the dopaminergic “on” state in patients with PD (at the same time, in each patient after the last session of conventional treatment). The dopaminergic “on” state refers to periods during which symptoms remain adequately controlled in response to dopaminergic medications. A flowchart describing the study design is presented in Figure 1.

The effectiveness of PA was assessed according to improvements in pain and related symptoms, changes in structural and functional brain data, and molecular signature indicators in blood samples. Previous studies have reported that structural and functional network topology on MRI differs between PD patients and healthy controls [16]. Therefore, healthy individuals were enrolled to undergo MRI assessment, and investigated the structural and functional MRI differences between PD and healthy controls. The study setting and site of data collection was the Clinical Trial Center of Kyung Hee University Hospital in Gangdong, South Korea. The study was designed and reported in accordance with the Consolidated Standards of Reporting Trials guidelines and the Standard Protocol Items: Recommendations for Interventional Trials (SPIRIT) checklist (Additional File 1). The protocol was reviewed, revised, and supported by experts on traditional Korean medicine, MRI, statistics, acupuncture, and neurologic disorders in South Korea.

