### 2.4. Randomization

The 90 patients were allocated to the PA, MA, or UC groups in a 1:1:1 ratio by an independent statistician using computer-generated three- or six-block-size randomization. Each participant was selected via systematic sampling and was assigned an identification code enclosed in an opaque envelope. The assessors were blinded to the primary outcome and the Unified PD Rating Scale (UPDRS) II and III scores. In other words, the assessors collecting the data were blinded to the group allocation. The outcomes were evaluated by two assessors, one of whom was blinded and one who was not blinded. The enrollment of participants, allocation sequence, assignment to groups, and assessor blinding were the responsibility of the Clinical Trial Center of Kyung Hee University Hospital.

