### 2.5. Interventions

All patients with PD underwent PA or MA therapy twice a week for 8 weeks. Conventional treatments, including L-DOPA, catechol-O-methyl transferase inhibitor, monoamine oxidase inhibitor, and dopamine agonist treatments, were allowed during the trial. For combination drugs, any drugs taken four weeks before participation in the study were allowed at the discretion of the researcher if they were not prohibited drugs (steroids, immunosuppressants, neuropsychiatric drugs) or other drugs that might have affected the results of the study. Analgesic drugs could be continuously taken if the dose had been stable for more than two weeks at the time of screening, but the details of drug administration (name of the drug, purpose of administration, dosage, and duration of administration) were recorded at each visit. In addition, any oriental medical therapy to improve PD pain, other than the intervention being performed in this study, was prohibited. Drugs that could affect symptoms during the period of clinical research were prohibited from being administered at the judgment of the researchers. Procedures, including details of needling (i.e., acupoints centered on the area where the participant complains of pain, needle stimulation, and retention time) to be administered in the PA and MA groups, were performed according to the clinical judgment of a senior Korean medicine doctor with more than 10 years of clinical experience based on the patient’s condition in the pragmatic randomized controlled trial (RCT). All procedural methods were retrospectively recorded. Treatment was discontinued based on the withdrawal of consent by participants or their legal representatives, violation of the eligibility criteria during the clinical trial, occurrence of adverse events (AEs), or poor compliance defined as receiving less than five of the sixteen total treatments.

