### 2.8. Outcome Measures

The primary outcome measure was the King’s Parkinson’s Disease Pain Scale (KPPS) score at visits 1 and 18 to evaluate the effectiveness of PA for pain in PD. Pain in PD has been previously divided into three types—PD-directly related pain (related to disease onset), PD-indirectly related pain (aggravated by the disease), and PD-unrelated pain [17]. The KPPS has been validated for PD-directly related pain. As subjects with KPPS score >0 were enrolled in this study, the effectiveness of PA was limited to PD-directly related pain. The secondary outcome measures were the numerical rating scale (NRS) score for pain area and questionnaire survey (UPDRS II and III, Beck Depression Inventory II, Beck Anxiety Inventory, Euro-Quality of Life-5 Dimension, Pain Catastrophizing Scale, and PD Sleep Scale-2) results for related symptoms. To investigate the biological mechanisms underlying PD, exploratory outcome measures included MRI findings, molecular signatures in the blood, SD questionnaire survey, gait analysis, and facial expression analysis based on facial muscle response to emotional stimulation. The schedule for outcome measure assessments is presented in Table 2.

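### The main effectiveness set is called a *complete set*; read literally this means completers, and it should be reworded to all randomised patients as allocated

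*Protocol article*

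**What the plan says.** Section 2.11.2 names two analysis sets in one sentence: "A complete set analysis was used to analyze the effectiveness of the intervention, and the per-protocol analysis was verified". The article defines neither set, and nowhere says that patients are analysed in the arm to which they were randomised.

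The next sentence gives the model (quoted without its last word): "For efficacy analysis, the mixed-effects model for repeated measures method was used, with each group and visit time as fixed factors and subjects as random".

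Four other places bear on the point:

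- **Section 2.2:** "This clinical study was a pragmatic randomized, usual care (UC)-controlled, three-arm trial". The Discussion defends this design on the ground that its results can inform everyday practice.
- **Section 2.4:** "The 90 patients were allocated to the PA, MA, or UC groups in a 1:1:1 ratio".
- **Section 2.5** lists the reasons for stopping treatment: withdrawal of consent, violation of eligibility, adverse events, and "poor compliance defined as receiving less than five of the sixteen total treatments". It speaks of treatment only. It does not say that assessment stops or that the patient leaves the analysis.
- **Table 2** schedules the KPPS at visits 1, 3, 10, 18 and 20. The post-baseline scores are therefore at weeks 4, 8 and 12.

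**The concern.** The article fixes its main effectiveness set with a term whose plain sense is patients with complete data. Its only other set is per-protocol. If the term is followed literally, three things go wrong.

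- **Randomisation.** Patients would be removed for reasons that arise after allocation. Those reasons need not be balanced. Usual care involves no needling, and the article describes no usual-care session, so the compliance rule and needling events would probably fall mainly on the PA and MA arms.
- **The model.** The main reason to fit a repeated-measures mixed model is that it uses the partial data of patients who miss visits. Fitting it to completers discards that benefit.
- **The check.** A per-protocol set tends to leave out the same kind of patient. Agreement between the two analyses would therefore say little about bias from exclusions.

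If the term was meant as the full analysis set, the cost is different: a reader cannot tell from the public text which analysis was prespecified.

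**Working it through.** The plan gives no figure of its own on the effect of the analysis set. Its nearest number, 30 per group in section 2.11.1, serves here only as the number randomised per arm.

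**1. The passages side by side**

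| Reading of the term | Repeated-measures model | Per-protocol as the check | Pragmatic aim |
|---|---|---|---|
| Completers | loses its main benefit | nearly redundant | conflicts |
| Full analysis set | fits | usual pairing | fits |

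The context leans towards the second row. The wording itself says the first.

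**2. Bias if completers are meant**

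Inputs, all assumed: no true effect; scores standardised, with higher meaning worse; correlation ρ = 0.6 between week 4 and week 8; the fraction d with the worst week-4 scores stops in one arm; losses in the other arm are unrelated to outcome.

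The mean week-4 score of those who stay shifts by m = φ(z)/(1 − d), where z is the (1 − d) normal quantile. The week-8 shift is ρ × m.

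| d | z | φ(z) | m | Completers-only bias, 0.6 × m |
|---|---|---|---|---|
| 10% | 1.282 | 0.1755 | 0.195 | 0.117 SD |
| 20% | 0.842 | 0.2800 | 0.350 | 0.210 SD |

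Simulation of the same mechanism gave 0.118 and 0.207 SD. A likelihood-based estimate from all available data had bias within 0.002 SD in both cases.

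Against the effect size assumed in section 2.11.1, 1.21, this is 0.117/1.21 = 10% and 0.210/1.21 = 17%. Against the effect detectable with 30 per arm (two-sided 5%, 80% power, about 0.74 SD by noncentral t), it is 16% and 28%.

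**3. The extreme case**

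If the patients with the worst week-8 scores themselves leave one arm, the completers-only bias is m: 0.195 or 0.350 SD. The mixed model alone then does not remove it. With v = 1 − z·m − m², the remaining bias is m(1 − ρ²)/(1 − ρ² + ρ²v):

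- d = 10%: v = 0.712, and 0.195 × 0.64/(0.64 + 0.36 × 0.712) = 0.14 SD.
- d = 20%: v = 0.583, and 0.350 × 0.64/(0.64 + 0.36 × 0.583) = 0.26 SD.

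Only continued assessment deals with this case.

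**4. When the first post-baseline score falls**

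Visit 3 is the first treatment visit and visit 18 the last, which makes sixteen. Visit 10 is therefore the eighth. A patient who stops coming before the fifth session, and is not assessed later, has no post-baseline KPPS. For such a patient the choice of model makes no difference, but continued assessment does.

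**5. Power**

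At an effect of 1.21, two-sided 5%, power is 99.6% with 30 per arm, 98.4% with 24 and 96.9% with 21. Under the plan's own inputs, the analysis set is a matter of bias and hardly of power.

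**The case against.** The strongest objection is that the article never says completers, complete cases or complete data. A reader might infer that patients who stop or miss visits are dropped from the primary comparison and that randomisation is therefore broken. The documents do not support that as fact. The term is undefined, it is paired with per-protocol as a full analysis set usually is, and the mixed model keeps partly observed patients. Section 2.5 stops treatment only. This objection stands, and it is why the point concerns wording that can be followed to a bad result.

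A second objection is that the imbalance between arms is uncertain. Withdrawal of consent and eligibility violations apply to every arm, and Table 2 schedules usual care alongside PA and MA and does not limit the compliance check to the needled arms. This also stands. The direction of any bias cannot be read from the article, so a claim that it favours PA would go too far.

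A third objection is that the illustration rests on chosen inputs. It does. The 0.195 and 0.350 SD figures need selection on the final outcome in one arm only and should not be quoted as the likely size.

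A last objection is that a condensed article may leave definitions to the full protocol or the SAP. That is fair for missing detail. Here, however, the article does state its main set, and does so with a term that points the wrong way.

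**Conclusion.** The point holds as a fault of wording with a real consequence if it is followed. The article names its main effectiveness set in a way that literally means completers, names per-protocol as the only check, and nowhere commits to analysis as randomised. Whether patients would in fact be excluded is not established.

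If completers are meant, a plausible size is about 0.12 SD at 10% loss and 0.21 SD at 20%, against about zero for the mixed model on all available data. This assumes no true effect, a correlation of 0.6, loss driven by week-4 scores in one arm, and loss rates that the article does not give. If the full analysis set is meant, there is no such bias from the set, and the fault is that the public text misnames it. The same short correction serves both readings.

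**What to change.** Replace the sentence in section 2.11.2 so that it says the following:

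- The primary analysis includes all randomised patients in their allocated arm and uses every available KPPS score in the mixed model.
- The KPPS assessments already scheduled at visits 10, 18 and 20 continue after study treatment stops, unless the patient withdraws consent for follow-up.
- Per-protocol and any complete-case analysis are supportive only.

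If the existing phrase was meant as the full analysis set, say so and define it in these terms.

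The cost is a few sentences and a little extra follow-up at visits that are already in the schedule. The estimate may turn out less favourable than one from completers.

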**Exclusion criteria**
Parkinson-plus syndromes (i.e., multisystem atrophy, progressive supranuclear palsy, corticobasal degeneration, and dementia with Lewy bodies)
Pain unrelated to PD (e.g., postoperative pain)
History of neuropsychiatric disorder unrelated to PD
Moderate or higher cognitive impairment that will interfere with the evaluation of treatment effects
Severe acute cardiovascular disease (i.e., heart failure, myocardial infarction, stroke, and hypertension)
Serious conditions (i.e., anemia, active pulmonary tuberculosis, thyroid disease, and other infectious and systemic diseases)
Active cancer
Uncontrolled hypertension (systolic blood pressure > 160 mmHg or diastolic blood pressure > 100 mmHg)
History of hypersensitivity reactions to PA
Indications for PA treatment being inappropriate or unsafe (i.e., hemorrhagic disease, patients with severe diabetes who have a higher risk of infection)
History of taking oral adrenal corticosteroids (steroids), immunosuppressants, or antipsychotic drugs or other drugs that may affect clinical trial results within the last 4 weeks
Inability to undergo MRI
Pregnant or lactating women or current contraceptive use among women of pregnant potential who are likely to become pregnant (except for women who have undergone sterilization)
History of drug or alcohol abuse
Unstable medical condition as determined by the research clinician; A patient who shows clinically significant diseases and disorders in physical or clinical examination or is receiving active treatment thereof
Participation in another clinical trial within the last 4 weeks
History of vaccination within 4 weeks or plans to be vaccinated during the clinical trial period
Inappropriate for enrollment due to other reasons as determined by the investigator

PD, Parkinson’s disease; PA, pharmacopuncture; MA, manual acupuncture; MRI, magnetic resonance imaging.

**Table 2 ijerph-20-01776-t002:** Schedule of enrollment, clinical outcomes, and safety assessment.

		Screening	MRI	Treatment			MRI	Follow-Up
Week		−2 to −1	−1 to −0	1	4	8	8 to 9	12
Visit No.		1	2	3 (Baseline)	10	18	19	20
Provide informed consent		O						
Identification of inclusion and exclusion criteria		O						
Demographics		O						
Medical and disease history		O						
Vital signs		O	O	O (every visit)	O (every visit)	O	O	O
Clinical laboratory examination		O				O		
Identification of eligibility criteria for MRI measurement		O						
Randomization		O						
Outcome measures	KPPS	O		O	O	O		O

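### The efficacy model as listed has no term for the visit-18 group difference in KPPS and no baseline adjustment; fitted literally to visits 1 and 18, its group effect is half the week-8 effect

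*Protocol article*

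**What the plan says.** The points below come from the protocol article.

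- **Model (section 2.11.2).** "For efficacy analysis, the mixed-effects model for repeated measures method was used". The terms of that model are then listed as follows: "with each group and visit time as fixed factors and subjects as random factors". The section names no group-by-visit interaction, no baseline covariate, no tested contrast and no set of visits for the response.
- **Primary outcome (section 2.8).** The KPPS "score at visits 1 and 18 to evaluate the effectiveness of PA for pain in PD". Visit 1 is the screening visit and visit 18 is week 8.
- **Assessments (Table 2, "Schedule of enrollment, clinical outcomes, and safety assessment").** KPPS is measured at visits 1, 3, 10, 18 and 20. Visit 3, not visit 1, carries the baseline label.
- **Other efficacy tests (section 2.11.2).** A paired t-test or "Wilcoxon signed rank test were used to compare factors before and after treatment within groups". These are not between-group comparisons.
- **Planning values (section 2.11.1).** "with a significance level of 5% and 80% power, the effect size was assumed to be 1.21", with 30 patients per group after an unstated dropout rate. Tests are two-sided (section 2.11.2: "values were two-sided").

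**The concern.** A model with group and visit main effects and a random subject term forces the difference between two arms to be the same at every modelled visit. Randomised arms do not differ in expectation before treatment. If pre-treatment scores are in the response, the single group coefficient therefore averages true zeros with the treatment effect.

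The stated endpoint makes this reading a natural one. It consists of one pre-treatment and one end-of-treatment visit. If visit 1 were removed from the response, only one visit would remain, and neither a visit factor nor a repeated measure would be left.

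The estimate is at stake more than the p-value. Section 2.11.1 describes a pilot meant to find out how much improvement PA can achieve. An estimate that is half the week-8 difference would mislead the larger studies that section 3 says it should inform.

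A second, separate matter is that baseline KPPS is available and the listed model makes no use of it to sharpen the comparison.

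**Working it through.** **Inputs from the document.** Effect size 1.21, two-sided 5%, 80% power, 30 per group, KPPS visits 1, 3, 10, 18 and 20, primary visits 1 and 18.

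**Assumptions.** The 1.21 is taken as the PA minus UC difference at visit 18 in units of the single-visit SD. The SD is equal across visits, the within-patient correlation ρ is constant (0.3, 0.5, 0.7), and no data are missing. KPPS at visit 3 is taken to precede the first treatment. The document gives no correlation and no time course of effect.

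**Step 1, the plan's own figure.** n per group = 2(1.960 + 0.842)² / 1.21² = 15.70 / 1.464 = 10.7, so 11 (12 with the t distribution). Going from 12 to 30 would need 60% dropout (12 / 0.4 = 30). The stated 30 is not reproduced from the stated inputs. The present point does not depend on that, and 30 per group is used below.

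**Step 2, what the group coefficient estimates.** In balanced data, with group and visit main effects and a random intercept, the coefficient is the plain mean over modelled visits of the visit-specific group differences. As a fraction of the visit-18 effect:

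| Visits in the response | Effect profile relative to visit 18 | Fraction | From 1.21 SD |
|---|---|---|---|
| 1, 18 | 0, 1 | 0.50 | 0.605 |
| 1, 3, 10, 18, 20 | 0, 0, 1, 1, 1 | 0.60 | 0.726 |
| same | 0, 0, 0.5, 1, 1 | 0.50 | 0.605 |
| same | 0, 0, 0.5, 1, 0.5 | 0.40 | 0.484 |
| 3, 10, 18, 20 | 0 at visit 3, then as above | 0.50 to 0.75 | 0.605 to 0.908 |
| 10, 18, 20 | 1, 1, 1 | 1.00 | 1.21 |
| same | 0.5, 1, 0.5 | 0.67 | 0.807 |

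A simulation of 5,000 balanced trials (ρ = 0.5) gave mean group differences of 0.60 for visits 1 and 18, and 0.72 for five visits with a constant post-baseline effect. Both agree with the algebra.

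**Step 3, power of the literal model on visits 1 and 18.** For m visits the SD of a patient's mean is √[(1 + (m − 1)ρ)/m]. SE = that SD × √(2/30), and power = Φ(effect/SE − 1.96).

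- ρ = 0.3: SD 0.806, SE 0.208, 0.605/0.208 = 2.91, power 83%
- ρ = 0.5: SD 0.866, SE 0.224, 0.605/0.224 = 2.71, power 77%
- ρ = 0.7: SD 0.922, SE 0.238, 0.605/0.238 = 2.54, power 72%

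With all five visits, profile 0, 0, 0.5, 1, 1 and ρ = 0.5: SD √(3/5) = 0.775, SE 0.200, 0.605/0.200 = 3.03, power 86%.

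**Step 4, power of a visit-18 contrast.** A group-by-visit term with baseline in the response estimates the difference in change, whose SD is √[2(1 − ρ)]. It recovers the full 1.21.

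- ρ = 0.3: SD 1.183, SE 0.306, ratio 3.96, power 97.7%
- ρ = 0.5: SD 1.000, SE 0.258, ratio 4.69, power 99.7%
- ρ = 0.7: SD 0.775, SE 0.200, ratio 6.05, power above 99.9%

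Using baseline KPPS as a covariate instead (SD √(1 − ρ²)) gives 99.8% or more throughout.

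**Step 5, separating the two issues.** Step 4 recovers the full effect without a covariate, so the missing covariate is not what halves the estimate. Its cost is precision: at ρ = 0.3 the SD is 1.183 for the change score against √(1 − 0.09) = 0.954 with the covariate.

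**The case against.** The strongest reply is that the halving is inferred, not stated. Section 2.11.2 does not say that the group main effect is the tested contrast, that pre-treatment scores are in the response, or that the response is the raw score rather than a change. Models of this class are often fitted with a group-by-visit term. Section 4 cites a full protocol, version 1.2, which is not at hand, and an article may leave interactions and covariates to it. This stands in part: the halving has to be stated as conditional. It does not remove the point, because the article does not merely stay silent. It lists the model's factors, and the list fits badly with the visit pair that section 2.8 names.

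Three stronger readings are tempting and are not supported:

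- **A reader might infer that the trial's power collapses.** With 30 per group, 80% power corresponds to about 0.72 SD (2.80 × √(2/30)). At 0.74 SD the literal model on visits 1 and 18 has only about 43%, 38% or 34% power (ρ 0.3, 0.5, 0.7). No effect of that size is in the document. At its own 1.21, literal power stays near the planned 80%, because 30 per group far exceeds what 1.21 needs.
- **A reader might infer that the missing baseline covariate causes the halving.** Step 5 shows that it does not.
- **A reader might infer that within-group p-values will be offered as proof of effect.** Section 2.11.2 names the mixed model for efficacy and lists the paired tests separately. Nothing says that they carry the conclusion.

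**Conclusion.** The point holds in conditional form. The model as listed has no term that isolates the between-group KPPS difference at visit 18, and it does not use the baseline KPPS that is collected.

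- **Fitted literally to visits 1 and 18:** the group effect is exactly half the week-8 effect, whatever that effect is. At 1.21 SD, power is about 83%, 77% or 72%, against 98% or more for a visit-18 change-from-baseline contrast.
- **Fitted to all five KPPS visits:** the fraction is about 0.4 to 0.6 under the profiles tried.
- **Fitted to post-baseline visits only:** no pre-treatment zero is averaged in, but weeks 4, 8 and 12 are pooled, giving 0.67 to 1.00 of the week-8 effect.

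The 0.50 for visits 1 and 18 needs only raw scores in the response, balanced data and the group main effect as the contrast. The five-visit and post-baseline fractions also depend on the assumed time course. The power figures rest on 1.21 being in single-visit SD units and on the assumed correlations.

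The defect concerns the primary between-group estimate and is worth correcting. The document does not show that a halved estimate will in fact be reported.

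**What to change.** Amend section 2.11.2 as follows:

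- Add the group-by-visit term.
- Adjust for baseline KPPS. Either use it as a covariate with post-baseline visits (10, 18, 20) as the response, or keep baseline in the response with group means constrained equal at baseline. The two are equivalent for this purpose.
- State which visit is baseline: section 2.8 uses visit 1, while Table 2 labels visit 3.
- Make the PA minus UC difference at visit 18, with its 95% CI, the primary estimate. UC is the control that section 2.2 puts in the design's description.
- Label the within-group before/after tests as descriptive only.

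If the full protocol or SAP already specifies this, bringing the article's sentence into line with it is enough. The cost is a few sentences and a few lines of SAS. No new data, visits or patients are needed.
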